Microclimate conditions within and around skin tissues strongly influence the tolerance of the skin to mechanical loading and shear [11]. For example, elevated temperature and humidity at the skin interface reduce the mechanical stiffness and strength of the skin [12] while also increasing its coefficient of friction [13]. These mechanisms can lead to a greater risk of tissue damage for the same mechanical stress [14,15]. In contrast, cooling reduces skin tissue’s metabolic demands and could increase the skin’s physiological tolerance to mechanical loads [12,16]. Early animal studies revealed that reduced skin temperature minimizes the risk of pressure ulcer formation [17,18]. This may occur through altered microvascular responses [18], as well as via downregulation of the expression of pro-inflammatory cytokines such as tumor necrosis factor α (TNFα), which is mediated by the stimulation of cold-sensitive transient receptor potential melastatin 8 (TRPM8)–expressing neurons in dorsal root ganglia [19,20]. Furthermore, our preliminary proof-of-concept experimental and modeling data on a representative skin site (the finger) indicated that skin cooling to 16 ºC can reduce friction by up to 35% for the same mechanical load [13]. This effect is likely due to changes in the viscoelastic properties of cooled skin tissues, which could in turn translate to reductions in shear stress. While this evidence highlights the potential therapeutic role of skin cooling for protecting tissue health, the mechanisms by which cooling enhances skin tolerance to pressure, shear, and friction remain poorly understood in humans [17-19,21-24].

In addition to its physiological effects, localized cooling of the skin can induce cold discomfort, which can limit acceptability and adherence to therapeutic interventions that promote skin integrity, particularly for vulnerable individuals at risk of pressure ulcers [25]. However, evidence on how the absolute temperature of a surface shearing against the skin contributes to thermomechanical discomfort is limited [26]. While the evidence above highlights the field’s limited mechanistic understanding of the effects of skin cooling on skin tissue viability, commercially available microclimate management systems, which deliver local and full-body cooling, continue to be developed and applied to support pressure ulcer prevention [27-29].

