**Figure 1 figure1:**
[figure not shown]
Experimental set up. The foot and ankle are supported by an orthotic brace and ankle support to standardize positioning while minimizing movement during the shearing protocol.

A series of measurements that run continuously or during discrete time points will be taken (Figure 2). First, baseline assessments, including structural and functional imaging of the posterior heel skin, will be captured using optical coherence tomography (OCT). This will be followed by sampling of skin sebum at the heel for subsequent biomarker analysis, using an established methodology involving a 2-minute application time and tweezer extraction to avoid cross contamination [38]. To provide an index of baseline local skin hydration, a capacitance meter will then be placed on the heel to measure skin conductance (in microsiemens). After the baseline measurements are completed, participants will place the heel on the thermal plate of the shearing rig [13]. The temperature of the aluminum thermal plate (22 × 16.7 cm) is controlled by a set of Peltier elements, and when applied to the skin, allows for the manipulation of local skin temperature (range 0 °C to >50 °C; variable temperature rates under PID control [Daisylab; MC Computing]). An optical fiber is integrated in the center of the plate through a 1-mm hole flush to its surface, allowing for the monitoring of skin blood flow via laser Doppler flowmetry (LDF) when the heel is static. An integrated force plate and low resistance trackway allow the recording of both normal and tangential forces (in newtons), respectively. The friction rig is interfaced with an analogue-to-digital data acquisition unit (MC Computing), sampling plate surface temperature (°C), normal forces, and tangential forces at 33 Hz. The kinetic coefficient of friction (CoF) according to Amonton’s law [39] can be estimated as the ratio of tangential to normal force and defined as the resistance generated from 2 surfaces rubbing against each other [40].

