The protocol starts by participants placing the heel in the center of the thermal plate over the hole, where the LDF optical probe is located flush to the surface. Positioning of the bed and lower limb will be modified to provide a standardized 15-N axial load on the plate. Skin blood flow will be measured intermittently (accounting for displacement of the heel following the static loading phases) throughout the protocol via LDF (moorVMS-LDF laser Doppler monitor; Moor Instruments). The heel will remain in place for a 60-second thermal preconditioning period to allow for temperature adaptation at the skin interface (at 36 °C, 24 °C, or 16 °C). The repeated shearing sequence will then commence (Figure 2), initially with a 10-second pause, before the servomotor travels in one direction pulling the rig and displacing it by 10 cm, pausing for 1 second, then traveling in the opposite direction, pushing the rig back to the original starting point. This sequence completes one repetition, which is repeated 10 times. After completing the 10 shearing repetitions, participants’ thermal perceptions will be recorded, followed by posttest OCT, skin sebum, and skin conductance measurements.

The sections below provide a description of the measurements to be used during the protocol.

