### Statistical Analyses

Data will be assessed for normality of distribution with the Kolmogorov-Smirnov test. Within- and between-subject mean differences (n=35 with 95% CIs) as a function of mechanical stimulus temperature (ie, 36 ºC, 24 ºC, and 16 ºC), time (ie, varying levels depending on the variables’ sampling rate), and participant group (ie, young, older, SCI) will be analyzed. These independent and interactive effects will be assessed by means of 3-way mixed model ANOVAs (or Friedman tests) for biomarker expression, skin structural properties, biophysical properties (ie, imaging parameters), subjective thermal perceptions, and kinetic CoF. Post hoc analyses will be performed between shear stimulus temperatures, time, and participant groups based on the presence of main effects and using the Tukey test. Group-related covariables associated with sex, skin tone, and clinical status (applicable to SCI participants only) will be considered in all analyses to interpret the proportion of variance unexplained by the main effects (ie, temperature, time, and group) and their interactions.

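### The named covariables are all person-level and cannot sharpen the within-person temperature contrast in kinetic CoF; the pre-plate skin conductance reading, already collected in each session, could.

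*Protocol article*

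**What the plan says.** All references are to the protocol article.

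- **Covariables.** Statistical Analyses lists kinetic CoF among the outcomes for the three-way mixed-model ANOVA (temperature, time, group) and adds that "Group-related covariables associated with sex, skin tone, and clinical status (applicable to SCI participants only) will be considered in all analyses". Their stated purpose is to help interpret variance that temperature, time and group leave unexplained.
- **Design.** Methods, Overview describes a randomised crossover with three plate temperatures, in three sessions at least 24 hours apart.
- **Hydration reading.** Experimental Procedures, in the text after Figure 1: "To provide an index of baseline local skin hydration, a capacitance meter will then be placed on the heel to measure skin conductance". The order follows: "After the baseline measurements are completed, participants will place the heel on the thermal plate of the shearing rig".
- **Friction.** In the same text, CoF "can be estimated as the ratio of tangential to normal force". Sliding begins only after the preconditioning step: "The heel will remain in place for a 60-second thermal preconditioning period to allow for temperature adaptation at the skin interface".
- **Link between moisture and friction.** The Introduction states that "elevated temperature and humidity at the skin interface reduce the mechanical stiffness and strength of the skin [12] while also increasing its coefficient of friction".

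**The concern.** Temperature is compared within a participant, across sessions. Sex, skin tone and clinical status do not change between one participant's sessions. Entered as main effects, they cancel from that comparison and cannot lower its error. For the randomised contrast, the named covariables therefore do nothing towards their stated purpose.

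CoF also lacks a baseline of its own. Biomarkers, imaging and conductance are all read before the plate. CoF exists only during sliding, after 60 seconds at the allocated temperature, so there is no pre-exposure friction value to adjust for. Pre-plate conductance is a session-level reading that the plate temperature of that session cannot have influenced, and it relates to a driver of friction that the Introduction names. Leaving it out of the CoF model may leave removable session-to-session noise in the error term. What is at stake is precision in one of several analysed outcomes.

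**Working it through.** **1. The plan's own figure.** The Participants section gives a minimum of 18 per group, up to 50% dropout and a target of 35. Check: 18 / (1 − 0.50) = 36, and 35 × 0.50 = 17.5. The target reproduces to within one participant. The 18 itself cannot be rebuilt, because the article gives no alpha, power, effect or SD. It rests on peak hyperemic response, not CoF. Both 18 and 35 are used below as group sizes.

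**2. Why person-level covariables drop out.** Write CoF for participant i in session j as: participant effect + b × (sex, skin tone, status)ᵢ + temperature effect + eᵢⱼ. In the difference between two sessions of the same participant, the participant effect and the b term vanish. The error is eᵢ₁ − eᵢ₂ whatever b is.

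**3. What a session-level covariate does.** Let r be the within-person, between-session correlation of pre-plate conductance with CoF. The documents do not give r, so it is an assumption shown as a range.

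- Residual variance factor: 1 − r²
- Standard error (SE) factor: √(1 − r²)
- Equivalent sample multiplier: 1 / (1 − r²)

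Power is for one paired temperature contrast within a group. It uses a noncentral t at two-sided alpha 0.05 (assumed), starts from 80% (assumed), and spends one degree of freedom on the covariate. The starting effect is 0.701 SD of the paired difference at n = 18 and 0.487 SD at n = 35.

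| r | Variance reduction | SE factor | Sample multiplier | Power, n = 18 | Power, n = 35 |
|---|---|---|---|---|---|
| 0.1 | 1% | 0.995 | 1.01 | 80.1% | 80.3% |
| 0.2 | 4% | 0.980 | 1.04 | 81.3% | 81.5% |
| 0.3 | 9% | 0.954 | 1.10 | 83.3% | 83.5% |
| 0.5 | 25% | 0.866 | 1.33 | 89.6% | 89.8% |

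**4. Simulation check.** A three-period crossover with participant effects and a session-level covariate (3,000 repetitions per setting) gave these ratios of adjusted to unadjusted SE:

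| r | n = 18 | n = 35 |
|---|---|---|
| 0 | 1.01 | 1.01 |
| 0.3 | 0.971 | 0.957 |
| 0.5 | 0.879 | 0.876 |

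These lie slightly above the formula, as expected when the slope has to be estimated. At r = 0 the price of adjusting is about 1% in SE.

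**5. Reach of the gain.** One conductance value per session acts on session-level error, and so on the temperature main effect. As a main effect it cancels from comparisons between repetitions within a session, so it does not sharpen the temperature-by-time interaction.

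**The case against.** The strongest reply is that this is only a helpful extra. The text names group-related covariables without saying that no others will be used, and a condensed article can leave session-level covariates to a fuller plan. That lowers the severity. It does not remove the point, because the article does state a covariable set for every analysis, and no member of that set can act on the randomised contrast.

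The second objection is to the chain of reasoning. The Introduction speaks of humidity where skin meets the surface. The candidate covariate is conductance before contact, in a room held at 50% relative humidity, ahead of sliding on dry aluminium. This stands as a caution: conductance is a proxy by short inference, and low values of r cannot be excluded.

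A reader might also infer more than the documents support:

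- **That the temperature effect is biased.** It is not. Temperature order is randomised and the reading precedes the plate.
- **That the group contrasts are confounded by hydration.** The second aim asks how biophysical pathways differ with aging and SCI. Hydration may be part of that difference, so an unadjusted group contrast is a legitimate target.
- **That the Discussion confirms the friction link.** Its remark that heat and moisture effects are well documented concerns the resilience of the epidermis. The friction link rests on the Introduction alone.
- **That conductance is the best available predictor of CoF, or that CoF is the study's central outcome.** Baseline imaging is also taken before the plate, and nothing ranks the two. The stated objective lists microvascular, inflammatory, structural and perceptual tolerance.

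**Conclusion.** The point holds as a cheap improvement of low severity. The named covariables cannot reduce the within-person error of the temperature contrast in CoF. A valid pre-exposure, session-level reading is already collected and is not assigned to that model.

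The size depends wholly on an unknown r. The effect is negligible up to r = 0.2 and becomes material only at values such as 0.5. The calculation assumes a linear relation on the analysis scale, the same slope at each temperature, and no carry-over from an earlier session's plate into a later session's conductance reading. The planned analysis remains valid without the change, and no large gain can be promised.

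**What to change.** 1. Prespecify, for the temperature contrasts in CoF, one added covariate: log pre-plate skin conductance for the session, expressed as the deviation from the participant's own mean over the sessions attended.
2. State that the post-shear conductance reading is never used for adjustment, because plate temperature can affect it.
3. Keep the young, older and SCI contrasts in CoF unadjusted as the main result. Report a hydration-adjusted estimate beside them, labelled as supplementary.
4. Record the choice before the CoF results are examined. The Results section says that data collection and analysis are ongoing, and a covariate added after results are seen would look data-driven.

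Cost: no new measurement, one degree of freedom, an SE about 1% larger if r = 0, and a second group estimate to report.

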## Results

Recruitment began in January 2024. As of February 2025, 43 participants have been enrolled in the study. Data collection and analysis are ongoing, and published findings are expected to be available in early 2026.

## Discussion

Prolonged mechanical loading from pressure, or pressure in combination with shear, over a bony prominence such as the heel can lead to skin damage and the formation of pressure ulcers [1]. Research that addresses the physiological tolerance of human skin to repeated mechanical shear is important for improving scientific knowledge and meeting societal demands. As such, this study protocol aims to investigate how cooling may influence the skin’s pathophysiological responses to repeated shear loading at the heel and how these responses may be modulated by aging and the presence of SCI. This study will provide a comprehensive understanding of the physiological processes and the potential benefits of cooling strategies to minimize the pressure ulcer risk at the posterior heel, while generating novel insights on temperature-modulated skin tolerance in vivo. This information will be relevant to skin physiologists, bioengineers, medical device manufacturers, and clinicians.

The study benefits from using a repeated measures design to purposefully sample clinically relevant groups of individuals and targeting relevant physiological and perceptual mechanisms. The heel is an anatomical location that contains minimal subcutaneous tissue, making it a vulnerable site for the development of pressure ulcers by impacting the integrity of the superficial layers of the skin [49]. The heel is particularly susceptible to injury in patients who are required to maintain semirecumbent positions, for example in bed, where individuals may repeatedly engage in repositioning (eg, from sliding down in bed) or transferring between support surfaces. Movement is often initiated by loading through the heels, creating both pressure and shear forces at the skin interface. Recent studies have shown how repeated pressure exposure, and pressure in combination with shear, elicits a biophysical and biomarker response from the skin [11,44,50,51] indicative of early signs of damage.

Previous animal data have shown that reducing skin temperature during applied mechanical loading could lower the metabolic demands of the underlying tissues, protecting metabolic and myogenic components of skin blood flow [23]. There is further evidence to indicate that lowering skin surface temperature can reduce the kinetic CoF [13]. In addition, the effects of both heat and moisture in decreasing the resilience of the epidermis in load-bearing regions of the body are well documented [52,53]. However, whether these findings from other anatomical sites translate to the skin of the heel, and how these mechanical interactions may lead to the risk of tissue damage, are unknown [10].

The study has been robustly designed but is not without limitations. Shear forces will be delivered via a dry aluminum interface, which may limit generalizability to clinical scenarios where the heel interacts with bedding with varying moisture saturation. The authors recognize the importance of evaluating the effect of temperature modulation of friction using patient-centered materials (eg, textiles used in the fabrication of chairs and beds), and the subsequent translation of clinically relevant findings. This research is currently being undertaken in our laboratory. Given the lack of data on localized cooling at the heel, identifying how the effects of skin cooling vary both physiologically and perceptually will therefore be important for developing bespoke patient-centered solutions to maintain skin integrity under shear stress that are both effective and comfortable.

## Appendix

Multimedia Appendix 1 Peer review report by the UK Research and Innovation (UKRI) Medical Research Council.

## Abbreviations

CoF: coefficient of friction
ELISA: enzyme-linked immunosorbent assay
ERGO: Ethics and Research Governance Online
IFNγ: interferon γ
IL: interleukin
LDF: laser Doppler flowmetry
OCT: optical coherence tomography
RA: receptor agonist
SCI: spinal cord injury
TNFα: tumor necrosis factor α
TRPM8: transient receptor potential melastatin 8
